### **Comparison arm training**

To maintain engagement in the trial, GPs and PNs (but not PSS) in the comparison arm were offered standard training (three hour seminar) in young people’s health covering youth friendly care, screening for health risks, organising appropriate professional networks for management of complex issues and medico-legal aspects of consulting with minors. They were provided with a small selection of further readings. This basic training is already widely available for GPs in Australia. Whilst there was informal group discussion during the seminar, the delivery was in a Power-Point lecture format with no active learning through role-play or group work.

### **Study design**

We used a stratified cluster randomised trial to test the effectiveness of our intervention. The trial was organised according to the Extension of CONSORT statement to cluster trials [58]. General practices were the unit of randomisation rather than individual GPs because the intervention involved changes to the office systems and training of clinicians and PSS at the same clinic. Ethics approval for all phases of the study was obtained from The University of Melbourne Human Research Ethics Committee.

The overall trial flow and phases (year two-five, 2007–2011) are depicted in Figure 2. The description of the measures is provided in Table 1.

**Figure 2 F2:**
[figure not shown]
**Flow chart of PARTY Project design.** Legend: GP = general practitioner; PN = practice nurse; PSS = practice support staff; YP = Young people **.** *42 practices were to be recruited allowing for 2 to drop out and 1200 youth allowing for a 40% attrition over 12 months.

#### ***General practice recruitment***

We required 42 practices to be recruited from metropolitan and inner regional centres in the state of Victoria, Australia (see sample size calculation below). Initially our inclusion criteria for practices stipulated that a core group of staff from various disciplines within the practice (GPs, PNs, practice manager and receptionists) were willing to participate. Within the first few months it became apparent that this requirement was hindering recruitment as interested GPs took extensive time to consult with PSS who were often too busy to have interest in research participation. Hence we accepted expressions of interest from practices when at least one GP was willing to participate. This GP later involved the key PSS.

Initially practices expressing interest were required to see at least 25 young people aged 14 to 24 years per week to be included in the trial, so that recruitment periods could be kept at three weeks. This inclusion criterion proved a barrier to participation in the study of many practices that were interested but found it difficult to calculate the number of youth seen each week. To overcome the practical difficulty, we modified our requirement and accepted practices if they perceived young people to be a significant part of their patient base.

Practices were not required to have a PN because at the time of initiating this study only 40% of Australian practices had a PN [59]. Without a PN, it was intended that the linkage function would be provided by a GP.

A diverse range of approaches were used to recruit general practices including: 

•direct mail out and telephone calls to all GPs within general practice divisions in all metropolitan areas and 4 regional areas within 1–3 hours of Melbourne

•advertisements in newsletters for the Royal Australian College of General Practitioners (RACGP) and general practice divisions

•direct mail out to the Victorian General Practice Research Network [60]

•direct mail out and telephone calls to all practices in a Medicare Australia randomly generated list of 250 Victorian practices (200 urban, 50 rural) seeing at least 25 young people 14–24 years per week (Medicare Australia is the major federal government agency responsible for administering health care payments, services and policies and has data on these parameters for every practice).

Practices were offered the following incentives for participation: 

•practice payment of A$1000

•continuing education points for participating GPs (a RACGP requirement)

•feedback of their patient data in aggregated form

•opportunity to benefit from advances in the evidence base for youth primary care.

Practices expressing interest were visited by study team members to explain the study fully. Consenting practices signed Consent Forms and a Memorandum of Understanding outlining the roles and responsibilities of practice and research staff. Practices were briefed on the procedures for recruiting young people and collecting denominator data for young people seen during the recruitment periods as well as on the processes for the ‘practice snapshot’ and the staff and parent surveys (see measures outlined in Table 1).

#### ***Recruiting and interviewing young people***

Young people were recruited into the trial in the ‘baseline profile’ and the ‘post-intervention’ phase (see Figure 2). The ‘baseline profile’ was collected prior to the randomisation of the practices to provide a snapshot of the young people seen by the clinician and to assess for baseline differences between the study arms after randomisation. The post-intervention sample of young people was a different sample from the baseline sample and became the study cohort followed up at 3 and 12 months.

a) Inclusion/exclusion criteria

All youth aged 14–24 years attending participating clinicians were eligible for participation. Exclusion criteria were: being physically or mentally (very) unwell (vomiting, febrile, weak, cognitively impaired or psychotic); unable to read or speak English; being under 18 years of age AND unable or unwilling to obtain parental consent AND judged by the clinician as incompetent to make an informed decision for participation in minimal risk research (that is, an immature minor) [61].

b) Recruitment and interview

Recruitment of young people into the study occurred in two phases. First, clinicians were trained to ask all eligible young people, after their consultation had finished, whether they would be willing for their contact phone number to be passed on to researchers for a full explanation of the study. GPs or PNs recorded telephone numbers of interested youth and any reasons for refusal or ineligibility; the clinicians were asked to fax this list to the researchers daily. The computer assisted telephone interview (CATI) staff telephoned all listed youth (usually on the same day) to fully explain the study and obtain formal consent. CATI staff then conducted the exit interview with consenting young people or made an appointment for the interview to take place at a time convenient for the young person. The interview (approximately 50 minutes long) could also be completed over several phone calls if not finished in one sitting. Young people were first notified by Short Messaging Service (SMS) to alert them that a call was coming from the project team. At the end of the interview, CATI staff obtained consent to telephone young people for the three month and 12 month follow-up periods. Follow-up interviews were approximately 20 minutes long. Young people had up to 20 telephone call attempts for up to two weeks before they were recorded as a missed recruit.

Young people, who completed a telephone interview, were given the option of entering a draw for an iPod valued at A$200 (drawn after each 500 interviews).

The data manager checked the numbers of youth recruited into the study against the total number of attendances at the practice that day, after retrieving the best possible information on this denominator figure from the practice software systems or manual counts. If the numbers of young people clinicians approached fell short of attendances, practices were phoned to offer assistance to improve recruitment.

Obtaining the total number of attendances at each practice each day was difficult because the typical appointment and consultation software used by practices is not designed to extract this information; many computer systems crashed when queries were run. Furthermore, rather than recording individual young people attending the practice, most appointment software systems capture the number of encounters, which may include one individual twice or more (e.g., when someone presents for a review). In addition, many nurse visits were not recorded electronically by practices.

The difficulty determining the total number of presenting patients over the data collection period is important in determining the representativeness of the study population compared to the whole population attending the participating clinicians and, thus, exactly how many young people might have been exposed to the intervention. The latter estimate is important for the economic evaluation. Sensitivity analysis will be conducted to explore the impact this may have on the findings of the study.

#### ***Baseline profile of young people***

Prior to randomisation of the practices, clinicians were instructed to recruit all eligible young people aged 14–24 years whom they saw within the two weeks baseline profile period. Clinicians completed a clinician encounter form (see Table 1) for each youth consult.

#### ***Baseline snapshot of staff and practice***

After baseline sampling of young people, the practice staff (participating GPs, PNs and PSS) were administered the staff survey and the research assistant conducted the practice snapshot visits. The purpose of this phase was to describe the baseline youth friendly characteristics of the practice; the self-perceived competency of participating staff in dealing with young people; and, to understand the way innovation is adopted within the practice.

#### ***Post-intervention sampling of young people and parents***

Eight weeks after randomisation and six weeks after the practice staff completed the intervention, practices recruited the young patients who formed the cohort followed up at three months and 12 months post-consultation. Clinicians were again instructed to recruit all eligible young people aged 14–24 years with whom they consulted until the required sample size for each practice was achieved. Parents attending with young people under the age of 18 years were instructed to complete the written parent survey and return it to researchers in a reply paid envelope. Clinicians again completed a clinician encounter form on each youth consult.

Our monitoring of recruitment rates of young people revealed that clinicians were failing to recruit continuously, and systematically; the timeframe for recruitment extended over long periods that varied from 13 days to nearly 11 months (mean 86.3 days). Within the longer periods, recruitment was inconsistent, influenced by practice constraints (e.g., accreditation activities, staff absence including extended sick leave as was the case for the practice which took 11 months). To complete the study within a reasonable timeframe and to ensure that all eligible young people were approached and recruited into the study, we changed our recruitment strategy for the last 15 practices by placing a research assistant in the waiting room to systematically approach every young person with an invitation to be involved. Slightly more intervention practices (8/19 intervention versus 7/21 comparison practices) received this assistance because recruitment in the intervention practices was delayed after randomisation due to longer times taken for training clinicians compared to the comparison practices. The additional benefit of the in-practice research assistants was the timely, daily transfer of phone numbers of eligible young people to the CATI interviewers and accurate recording of reasons for refusal to participate or ineligibility.

#### ***Follow-up at three and 12 months (year two-five)***

Youth from the post-intervention sample were called by CATI staff for their three month and 12 month follow-up interviews. The three month interviews were completed by November 2010 and the 12 month interviews were completed by the end of July 2011.

#### ***Post-intervention interview with practice staff***

As part of our process evaluation, semi-structured interviews with GPs, PNs and PSS were undertaken for both study arms three months post-intervention to determine the acceptability of their respective screening methods and whether any practice changes were sustained. The clinician encounter forms on each patient consultation along with the young person’s exit interview also contain data that will capture the extent to which the intervention was implemented as intended.

#### ***Randomisation***

The randomisation of practices was stratified by postcode level advantage-disadvantage scores (SEIFA - Socio-Economic Indexes for Areas) for Victoria in 2001 [62] (dichotomised into low versus middle/high tertiles) and type of practice (private billing, bulk billing, and community health centres) forming 6 strata. Bulk billing practices do not charge patients for the consultation but accept only the fixed national health care rebate for the consultation specified by the Australian government. These strata were chosen because young people from lower socio-economic areas are more likely to consult bulk-billing practices and are more likely to have psycho-social health risks [5]. Block randomisation with fixed block sizes of two was used within strata. Randomisation was carried out by an independent statistician not connected with the trial. The independent statistician informed the project manager (BG) of the randomisation result and the practices were informed after all their baseline profile data collection was completed. The allocation sequence remained concealed from the research team until all practices entering the trial had their interventions assigned.

#### ***Blinding***

Due to the nature of the intervention it was not possible to blind the practices to their study arm status. The CATI staff and the in-practice research assistants who recruited patients into the trial were blind to the study arm status of the practices. Young people were not informed of the intervention status of their practice in any written or verbal communication from the researchers. It is unknown whether practice staff may have inadvertently informed patients about the study arm status of the practice.

#### ***Sample size estimation***

Sample size calculations assumed 80% power at a significance level of 5% for two- sided test and an intra-clinic correlation of 0.04 [63]. The original first hypothesis was based on the assumption that 40% of youth attending general practice have health risk behaviours or emotional distress, and that trained GPs, at best, will pick up 60% with interview alone [17], equivalent to 24% of all presenting youth. For a clinically meaningful outcome, we expected the clinicians to detect a further 25% of youth with risk taking behaviours using the screening tool with the interview (intervention arm), equivalent to an additional 10% of all presenting youth to the practice, compared to the comparison arm. To detect a 10% difference in the clinician’s detection of risk taking behaviours of all youth attending general practice between the two study arms, 1760 youth (44 per practice in 40 practices) were required after allowing for a variance inflation factor (VIF) of 2.72.

To allow for the slow recruitment rates, we revised our intended intervention effect in the clinician’s detection of risk taking behaviours of all youth attending general practice from 10% to 12.5% (equivalent to intervention clinicians picking up a further 31% of youth with risk taking behaviours instead of the 25% originally proposed). This small adjustment to the effect size reduced the required sample size to a total of 720 youth (18 per practice in 40 practices with a VIF of 1.68). To allow for a 40% loss to follow-up of youth over 12 months [64], we calculated that a total of 30 youth in each practice needed to be interviewed at recruitment. An additional two practices were also recruited to allow for loss of practices during follow-up.

The revised sample size also affects the difference in the prevalence of the risk behaviours that can be detected between the study arms in the second hypothesis. Table 2 gives the minimal effect size that can be detected in the prevalence of selected risk behaviours between the study arms at 3 and 12 months follow-up (power 80%, alpha 5% for a two-sided test) for the revised sample size for a range of intra-cluster correlations. The revised sample size is sufficient to detect at least a 15% difference between the two study arms for each of the risk behaviours with 80% power and alpha at 5% for a two-sided test.

**Table 2 T2:** Minimal effect size that can be detected for the revised sample size given comparison arm risk behaviour prevalence, for a range of ICCs*

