The second amendment, made soon after recruitment of patients had begun, was to change the absolute percentage effect size shown in hypothesis one and two, to 31% and 15%, respectively. The minimum detectable effect sizes were modified in response to the slow recruitment rate of young people because the original sample size required to detect smaller effect sizes was unattainable within the time frame and resources available to conduct the study (see section on sample size estimates).

Hypothesis four, about the intent to conduct an economic analysis from a societal perspective, was amended during the study pilot to instead conduct the economic analysis from a health care perspective only. The societal evaluation approach requires the estimation of a monetary valuation of benefits. In addition to the large sample sizes required for such an analysis, there would have been a considerable responder burden as young people would already have been surveyed with a long interview for the main health outcomes.

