Staff survey	Likert scales and demographic survey	Self-perceived competency with youth friendly care and managing young people's health risk. Demographic data on age, gender and for clinicians, year of graduation, prior training in youth health or brief interventions and timing of these.	Self-completion written questionnaire	Baseline profile and post-intervention
Staff interview	Semi-structured interview	Acceptance of screening processes	Qualitative interview with RA, audio-taped	3-month follow-up phase
Nurse interview	Semi-structured interview	Feasibility of role in screening, counselling and linkage function	Qualitative interview with RA, audio-taped	3-month - 12 month follow-up phase
*Young people’s exit interview*				
Recall of Screening and Counselling [83]	Self-report categorical responses	Recall (occurring with healthcare provider) of screening/counselling for health risk	Computer Assisted Telephone Interview (CATI)	Baseline profile and post-intervention
GPAQ [84]	Self-report categorical responses			
Family Doctor Trust Scale [85]	Self-report categorical responses	Items related to trust in the clinician		
Likelihood of Future Visits Scale [86]	Self-report categorical responses	Items examining what conditions youth happy to see the clinician about		
Recall of other youth friendly processes	Self-report categorical responses	Confidentiality discussion, time alone with clinician		
K10 [87]	Self-report likert responses	Emotional distress		
Self-rating of mental and physical health [88]	Self-report categorical responses			
	SF12 [89]	Self-report likert responses	quality of life		
DEP-ADO [90,91]		Self-report categorical responses	Smoking, alcohol and other subtance use		
Abuse Screen [92]	Screening adolescents for abuse	Fear of a partner, fear of a family member for those 17 yrs and over			
Other risky behaviours/events	Self-report categorical responses and some likert scales	Unprotected sex, forced sex, road safety risk, eating and exercise Patterns, self harm, antisocial behaviour, bullying events.			
Considering risky behaviour change	Self-report binary yes/no response for self-identified risk				
Readiness for Change Ruler [93]	Self-report likert scales	Readiness for change			
Intention to Change [93]	Self-report catgeorical responses on a 5 point agree/disagree scale	Consideration of change			
Health service use	Self-report categorical responses	Use of a wide range of health services and costs			
*Young people's follow-up interviews*					

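### The revised 12.5-point (31%) detectable effect for hypothesis 1 rests on the 720 youth expected after 12-month attrition, although detection appears to be measured at the consultation on all 1200

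*Protocol article*

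**What the plan says.** The Sample size estimation section of the protocol article states: "Sample size calculations assumed 80% power at a significance level of 5" (per cent, two-sided), with "an intra-clinic correlation of 0.04". It takes it that "40% of youth attending general practice have health risk behaviours or emotional distress" and that trained GPs find 60% of them by interview alone, "equivalent to 24% of all presenting youth". The original target was a further 25% of at-risk youth, that is 10 points of all youth. It needed 1760 youth (44 per practice in 40 practices, VIF 2.72), and no allowance for loss to follow-up is mentioned.

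Because recruitment was slow, the target became 12.5 points of all youth (31% of at-risk youth). The section says this "reduced the required sample size to a total of 720 youth (18 per practice in 40 practices with a VIF of 1.68". Then, to allow for 40% loss over 12 months, "a total of 30 youth in each practice needed to be interviewed at recruitment". The legend of Figure 2 gives the total as 1200.

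Under Study questions, the second amendment "was to change the absolute percentage effect size shown in hypothesis one and two, to 31% and 15%, respectively", and the article calls these revised values minimum detectable effects. It was made soon after patient recruitment had begun.

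Table 1 lists, in the young people's exit interview, "Recall (occurring with healthcare provider) of screening/counselling for health risk", and separately a form that the clinician completes after each consultation. Both are scheduled for the baseline and post-intervention phases. The 3- and 12-month interviews cover risk behaviour, K10, SF12, abuse and violence, service use, and whether the clinician's advice was followed up. They do not cover detection.

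**The concern.** Loss over 12 months cannot remove a young person from an outcome recorded at the consultation that brought them into the study. If detection is taken from the exit interview or the encounter form, hypothesis 1 is tested on everyone interviewed at recruitment, planned as 30 per practice. The 18 per practice is the number expected to remain for the last follow-up of hypotheses 2 and 3. A single base has been used for both kinds of outcome.

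This matters because the 31% replaced a registered 25% in the hypothesis itself, on the ground that the sample for the smaller effect could not be reached. A reader comparing 1760 with 720 sees a sample reduced by more than half. For an outcome measured at the consultation the comparable figures are 1760 and 1200. The article describes the 25% effect as clinically meaningful, so readers should be able to see how much power the planned sample kept for it.

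**Working it through.** **Inputs, all from the protocol article.** Two-sided 5%, 80% power, ICC 0.04, 40 practices (20 per arm), comparison-arm detection 24% of all youth, at-risk prevalence 40%. Cluster sizes: 44 (original), 18 (revised, after loss), 30 (at recruitment).

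**Formulas.** Individually randomised n per arm, pooled variance, no continuity correction, with p̄ the mean of p₁ and p₂:

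n = [1.96·√(2p̄(1−p̄)) + 0.8416·√(p₁(1−p₁)+p₂(1−p₂))]² / (p₂−p₁)²

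VIF = 1 + (m−1)·ICC; effective n per arm = 20m/VIF; m needed = n(1−ICC)/(20 − n·ICC).

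**1. The plan's own figures.**
- Original, 24% v 34%: n = 323 per arm. m = 323×0.96/(20−12.92) = 43.8, so 44 per practice and 1760 in total. VIF = 1+43×0.04 = 2.72. Matches.
- Revised, 24% v 36.5%: n = 211 per arm. m = 211×0.96/(20−8.44) = 17.5, so 18 per practice and 720 in total. VIF = 1+17×0.04 = 1.68. Matches.
- Inflation: 18/0.6 = 30 and 720/0.6 = 1200. Matches.
- Conversion to at-risk youth: 10/40 = 25% and 12.5/40 = 31%. Matches.

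So 1760 reproduces with no attrition allowance, and 720 is a number before inflation for attrition.

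**2. Which outcomes 720 fits.** Solved as decreases at 18 per practice and ICC 0.04, the detectable differences from 41%, 38% and 24% are 12.8, 12.6 and 10.5 points. Table 2 gives 13, 13 and 10. Table 2 is therefore built on 18 per practice, which suits outcomes that suffer the 12-month loss.

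**3. Hypothesis 1 on the planned exit sample.** m = 30: VIF = 1+29×0.04 = 2.16; effective n = 600/2.16 = 277.8 per arm.

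- Detectable difference: at 24% v 34.8%, the formula gives (1.2628+0.5384)²/0.108² = 278, so about 10.8 points, and 10.8/40 = 27% of at-risk youth. With a continuity correction it is 11.2 points (28%).
- Power for 12.5 points: z = (0.125×√277.8 − 1.2732)/0.6436 = 1.259, which is 89.6%.
- Power for 10 points: z = (0.10×√277.8 − 1.2578)/0.6378 = 0.641, which is 73.9%.

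**4. Across the ICCs of Table 2, 30 per practice, same formulas.**

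| ICC | VIF | Effective n per arm | Detectable difference | Power, 10 points | Power, 12.5 points |
|---|---|---|---|---|---|
| 0.01 | 1.29 | 465.1 | 8.3 points | 92% | 99% |
| 0.04 | 2.16 | 277.8 | 10.8 points | 74% | 90% |
| 0.07 | 3.03 | 198.0 | 12.9 points | 59% | 78% |

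For comparison, 18 per practice at ICC 0.04 (effective n 360/1.68 = 214.3) gives 12.4 points, 63% power for 10 points and 81% for 12.5. Splitting the practices 19 v 21, as reported in the article, leaves the 30-per-practice powers at 89.6% and 73.9%.

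**The case against.** The strongest reply is that nothing was miscalculated. The article chose an effect, derived 720 from it correctly, and inflated correctly to 1200. One cohort serves an outcome at the consultation and outcomes at 3 and 12 months, and sizing recruitment to survive the longest follow-up is ordinary planning. For hypothesis 1 it yields more power than claimed at the plan's ICC. Nor does 25% or 31% enter the analysis: the Data analysis plan reports odds ratios with 95% confidence intervals and p-values. Data collection had finished and analysis was under way when the article was written.

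All of that stands. A reader might infer from the mismatch that 720 or 12.5 points is an arithmetical error, or that a sample was cut by attrition to arrive at 31%. The documents support neither: every figure reproduces, and the order was effect, then 720, then 1200.

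Two limits also stand. The article does not name the instrument that defines detection, so its timing is inferred from Table 1. And 1200 is a planned number; the number actually interviewed is not given.

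What the reply does not answer is that the article presents 31% as a minimum detectable effect and uses it to replace a registered value. For the planned exit interviews, that description is not correct.

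**Conclusion.** The point holds as a fault in the sample-size basis for hypothesis 1, of minor to moderate weight. At ICC 0.04 the planned 1200 exit interviews detect about 10.8 points (27% of at-risk youth) with 80% power, where the article gives 12.5 points (31%). Power for 12.5 points is about 90%, not 80%. The mismatch is therefore conservative at the plan's ICC; at 0.07 power for 12.5 points would be about 78%.

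It would be going too far to say that the amendment was unnecessary. The registered 10 points keeps only about 74% power at 1200 and needs 1760 for 80%. Some relaxation was required, but less than the article states.

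The result assumes that detection is taken from the exit interview or encounter form, that 30 youth per practice were interviewed in 40 practices, and that the 24% comparison rate holds.

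**What to change.** In the sample size section, separate the two bases.

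- For hypothesis 1, state the detectable difference and power on the planned 1200 exit interviews, or better on the number actually interviewed: VIF 2.16, about 10.8 points (27% of at-risk youth) at ICC 0.04, 8.3 to 12.9 points over ICC 0.01 to 0.07, and about 90% power for 12.5 points.
- Beside it, show the registered 25% effect with its power of about 74%, so that readers can see how far the amendment was forced by recruitment.
- Keep 720 (18 per practice) and Table 2 for the 12-month outcomes only.
- Say which instrument defines detection and when it is completed.

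Do not write a third effect size into hypothesis 1 after data collection; the registered and amended values should stand as the record. The cost is a few sentences, with no new data and no change to the analysis.
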